### Who will take informed consent? {26a}

The phone screen step includes a Consent Process Documentation for Phone Screen completed by the research assistant performing the phone screen, which documents the potential subject verbally consented to participate in a phone screen for the project. Those eligible on phone screen are invited to the diagnostic interview (SCID-5-RV). In the interim, they are sent an appointment reminder and an electronic version (PDF) of the informed consent document to review. The P.I. and graduate student research assistants who conduct the diagnostic interviews are the ones who seek informed consent. When the potential subject presents, we first go over the informed consent document in detail and answer any questions. We explain that participation is voluntary and they may decline to participate, take more time to think it over, or consent and proceed with the diagnostic interview. If they decide to consent, the subject and P.I. or designee both sign and date the consent document and proceed with the diagnostic interview. We then complete a Consent Process Documentation form for this protocol. The consent form was completed in paper form from during the fall/winters of 2018-2019 and 2019-2020. Effective for the fall/winter of 2020-2021 and beyond, due to the COVID-19 pandemic, we used HIPPA-compliant videoconference to review the consent form with potential volunteers and obtained written consent via REDCap electronic data capture tools hosted at the University of Vermont.

### Additional consent provisions for collection and use of participant data and biological specimens {26b}

This trial does not involve collecting biological specimens for storage.

## Interventions

### Explanation for the choice of comparators {6b}

The CBT-SAD protocol used in this study is justified because it is the only psychotherapy treatment for SAD with data to support its efficacy. The comparator LT condition is justified because LT is the established acute SAD treatment. Antidepressant medications represent another first-line SAD treatment; however, this trial was funded under an FOA focused specifically on confirming the efficacy of non-pharmacologic treatments. Although some people might rather be in a trial where there is the possibility of receiving the combination of CBT-SAD and LT, administered concurrently, we did not include a combination arm in the design. This is based on our prior study that tested the combination of CBT-SAD+LT against solo LT, solo CBT-SAD, and a wait-list control group. All three active treatments improved winter depression symptoms as compared to the wait-list control over 6-weeks, with no significant differences between them [43]. However, at follow-up the next winter, solo CBT-SAD was superior to solo LT on recurrences and depression severity, and these differences survived adjustment for re-treatment in the interim [44]. In contrast, the combination group was superior to solo LT only on recurrences, and this difference became non-significant after adjusting for re-treatment [44].

### Intervention description {11a}

#### Timing of the treatments

Given SAD’s inherent seasonality, recruitment will begin September 1 and participants will be enrolled on a continuous basis as they qualify. The second week of February will be the latest treatment start date. Similar timing procedures worked successfully in our prior studies. Our data suggest that the treatment groups grew at comparable rates over time with no significant differences in the timing of treatment initiation or cessation between the groups, and that treatments were completed during the winter.

#### Cognitive-behavioral therapy (CBT-SAD)

The P.I. (K.J.R.) tailored traditional CBT for depression to address the special needs of the SAD population in developing the “Coping with the Seasons” protocol and its manual [11]. CBT is placed in a seasonality framework with the rationale addressing the role of environmental changes as well as cognitions and behavior in symptom onset/maintenance. Traditional CBT elements of behavioral activation and cognitive restructuring are framed as ways to improve coping with winter. Some cognitive restructuring specifically focuses on challenging negative thoughts related to the winter season, light availability, and weather. A recurrence-prevention component addresses early identification of negative anticipatory thoughts about winter and SAD-related behavior changes, using the CBT skills learned to cope with future winter seasons, and development of a personalized relapse-prevention plan. As in prior studies, the CBT-SAD protocol includes 90-min. CBT sessions twice a week over 6 weeks (total of 12 sessions and 18 h) in small groups (typically 4–8 patients per group). CBT-SAD sessions were conducted in-person until March 2020, when we moved them to HIPPA-compliant video conference platform due to the COVID-19 pandemic. In our prior R01, CBT-SAD attendance was quite good, mean = 9.1 sessions (SD = 3.5). Seventy-three of 88 (83%) attended 7 or more sessions, and 56/88 (64%) attended 10–12 sessions. To accommodate unpredictable schedules, if a patient misses a session, there is opportunity to “catch-up” with group facilitator before the next session and to make up the session in another concurrent CBT-SAD group; both are documented.

#### Therapists

Six trained clinical psychology graduate student research assistants will facilitate the CBT-SAD groups, supervised by the P.I. (K.J.R.). Each group will be led by a pair of group facilitators. The P.I. will provide therapists with session-by-session training in the manual content prior to their providing any treatment. Subsequently, PI [name] will review audiotapes of each CBT-SAD session and will discuss these sessions in weekly 1-h group supervision meetings with each pair of facilitators focused on [1] discussion of general issues in therapy, participant progress, and the treatment protocol, and [2] the P.I. providing detailed feedback on the prior two sessions. Supervision and training meetings occurred in person until March 2020 when we shifted to videoconference due to the pandemic, with all parties participating from a private office to protect confidentiality. These training procedures were successfully used to train two community therapists in our prior R01 study, with no significant differences between P.I. [name] and the other two therapists in post-treatment outcomes (all ps > .50). The multi-component supervision protocol reflects what works best in the field [45].

#### Light therapy (LT)

Participants attend an initial instructional session that follows a script to explain the treatment rationale and assembly/position of the light box. These will be conducted by the (unblinded) P.I. in small groups of 2–4 subjects for efficiency. Effective fall/winter of 2020–2021, the P.I. posted a video recording of the instructional session on the lab’s private YouTube channel for those randomized to light therapy to watch remotely, due to the COVID-19 pandemic. In their homes, LT participants will use the SunRay (SunBox Company, Gaithersburg, MD), a standard device (23” × 15½”× 3¼”) with an ultraviolet shield that emits 10,000-lux of cool-white fluorescent light to the retina when the user is within 18 inches. Each of the 6 weeks, participants will complete the Light Therapy Side Effects Questionnaire used in our prior studies to assess the presence and severity of any side effects attributed to LT and self-reported times for onset of sleepiness, onset/offset of actual sleep, and desired times for onset/offset of sleep over the previous week. Side effects associated with LT are generally mild and can include headache (19%), eyestrain (17%), and feeling “wired” (14%) [46]. Although individuals typically respond within 4 weeks of initiating LT or not at all [16], our LT protocol will be maintained for 6 weeks to match CBT-SAD’s duration. To circumvent ethical concerns of discontinuing LT during the winter (when relapse is likely) [1], participants are encouraged to keep using the light box and bring it to the lab for servicing in May (to check the bulbs against a photometer and download adherence data). In an effort to reduce access to a suitable device as a potential confound, we will offer access to our light boxes to LT participants in winters 2 and 3 and to CBT-SAD participants crossed into LT in winter 2 for use in winter 3.

During each week of LT administration, the P.I. will contact Co-I (T.T.P.) via phone to review each LT subject’s weekly SIGH-SAD scores to date and responses on the Light Therapy Side Effects Questionnaire. We successfully used this type of telephone supervision for the LT condition in our prior studies. Because direct comparisons show morning LT is a more potent antidepressant than evening LT [15], and as articulated above, it is assumed that that morning light manifests its effects via correcting a pathological circadian phase-delay in SAD, we will initiate LT at 30-minutes in the morning, first thing upon awakening, to be completed between the hours of 0600 and 0900 (i.e., in the phase advancing portion of the phase response curve to light) [47]. After the first week, [name] will recommend individually tailored adjustments to the duration of light use per our treatment algorithm to maximize response and reduce any reported side effects. Incremental changes in the duration of LT are initiated upon an insufficient response to light, defined as a < 30% reduction in SIGH-SAD at the end of week 1, < 50% reduction in SIGH-SAD at the end of week 2, or not fulfilling SIGH-SAD remission criteria at the end of week 3 and beyond. In these cases, if the side effect profile permits, the duration of LT is increased in steps of 15 min/day up to a maximum of 2 h/day. Decrements in LT are based on side effects and consist of decreasing the duration of LT in steps of 15-min/day. LT is temporarily halted for severe side effects (e.g., severe migraines) and restarted the following day with a reduced duration (50%), which is slowly increased to tolerance.

There are two concerns related to circadian phase-shifting induced by light: side effects of the phase-shift and reduced antidepressant effectiveness if addressing the phase-shift. In a re-analysis of Eastman et al.’s data [23], evening light treatment for SAD phase-delayed and morning light treatment phase-advanced the temperature minimum (Tmin) by 1 h [48]. Early awakenings and/or late afternoon or early evening sleepiness sometimes reported by patients could be the result of a circadian phase-advance induced by the morning administration of LT. If this occurs, the duration of the morning LT is reduced (if side effects present) and/or adjunct evening light is added. The P.I. will contact LT participants to convey any recommended changes to their LT prescription. These procedures for weekly adjustments to the daily duration of LT replicate those used in our previously completed R01.

### Criteria for discontinuing or modifying allocated interventions {11b}

We have operationalized decision rules to identify any participant who is escalating in severity during the acute treatment phase that will be uniformly applied across treatment conditions. These subjects will be removed from the treatment protocol and referred for SAD treatment outside the study. First, any participant who demonstrates one of the serious adverse events described below (i.e., serious side effects to light therapy, mania or hypomania, or significant suicidal intent) will be removed from the treatment protocol. Second, participants who fall outside of the acceptable range for increasing SIGH-SAD scores (i.e., an increase of 12-points or more over pre-treatment SIGH-SAD score) for 2 consecutive or nonconsecutive weeks over the treatment phase will be removed from the treatment protocol. To operationalize this definition, we used prior data to generate the means and variability for the weekly SIGH-SAD scores for concurrent wait-list controls during the 6-week waiting phase when they were untreated [43]. The means and SDs were relatively consistent over the 6 weeks; therefore, we calculated the mean SIGH-SAD and its SD over the 6-weeks for the WLC condition (24.48 ± 5.78). Therefore, a 12-point increase over pre-treatment SIGH-SAD indicates a SIGH-SAD score that is 2 SDs above the typical variance observed for our wait-list controls. The reason that we specify 2 weeks is to minimize the chance that a temporary stressor contributed to a temporary exacerbation as opposed to a true treatment nonresponse. Even if removed from protocol, we will include all cases in the analysis and we will attempt to collect data from all participants, at each time point as the primary analysis is an intent-to-treat analysis of all randomized cases.

Related to these two instances where we will remove a participant from the treatment protocol are cases where participants initiate outside treatment on their own during their study treatment. To assess the initiation of treatments outside of the study, we have added relevant questions to the beginning of each SIGH-SAD assessment. We will uniformly ask the question, “Have you started any new treatments outside of the treatment you are receiving in this study such as light therapy, talk therapy, or medications?” If a participant responds affirmatively, they will be queried by the interviewer for the details of this non-study treatment, which will be recorded. If a new treatment has been initiated, these cases will uniformly be considered as withdrawn from treatment protocol.

Study records include SIGH-SAD scores at each timepoint for each participant in the study. The project coordinator will monitor these records weekly to determine if any participant has met the criteria for protocol withdrawal. The PI will refer these cases for more intensive individual treatment from a local provider with training in treating SAD/depression. The project coordinator will also monitor weekly responses to the queries about initiating a new, non-study treatment to detect any treatment failures. Participants are informed that their progress over the study will be closely monitored; and, if at any time symptom severity escalates, the P.I. will discuss with them the possibility of referral for outside treatment.

To summarize, participants who experience a severe adverse event or meet our criteria for an excessive exacerbation in SIGH-SAD score during treatment will be removed from the treatment protocol and referred for outside treatment. Participants who decide to seek any outside treatment on their own will be coded as voluntarily withdrawn from protocol. According to intent-to-treat (ITT) principles, such participants will be encouraged to attend ongoing study monitoring (SIGH-SADs) to gauge their symptom severity and to participate in the follow-ups per the study assessment schedule. They will be included in ITT analysis as randomized, and also analyzed in an actual-treatment analysis. If initiation of outside treatment occurs, this event will be coded for in the database. Decisions about whether to consider this as a moderator of outcome, will be made in consultation with the Co-I study biostatistician (P.M.V.) based on how frequently this event occurs.

### Strategies to improve adherence to interventions {11c}

#### Patient adherence to treatment

Patient adherence to CBT-SAD will be assessed via session attendance. Each therapist will keep a session attendance record, submitted to the Project Coordinator at the end of each treatment week. If a participant misses a CBT-SAD session, the group facilitators attempt to contact them prior to the next session to discuss their absence and encourage continued attendance. In addition, each therapist will keep session-by-session records of homework completion (0 = no homework, 1 = partial completion of homework, 2 = completion of homework). Beginning in session 2, each CBT-SAD session includes a thorough review of the homework assigned at the end of the prior session. To assess homework completion from the patient perspective, weekly during the 6 treatment weeks, CBT-SAD subjects will rate their frequency of completing the homework assignments, on average, over the past week on a 5-point scale (0 = never, 1 = less than 1 day per week, on the average, 2 = 1 day per week, on the average, 3 = 2 or 3 days per week, on the average, 4 = more than 3 days per week) [49].

Adherence to the LT prescription will be objectively monitored with a data logger to monitor time turned on and the duration before being switched off. Data will contain time and date stamps. When returned to the lab, data will be downloaded by USB connection to PCs for analysis. Data will be sampled every second to minimize the need for data reduction. During active LT, each participant is asked to keep a diary of light therapy use to document state and end times by date so the P.I. can track self-reported compliance each week. If a participant reports light therapy durations that are shorter than what was recommended, the P.I. will contact them to discuss it and encourage using LT at the currently prescribed duration to maximize efficacy. We also hold-off on making a weekly LT duration increase if the participant has been compliant with the current dose and instead attempt to address compliance.

#### Treatment integrity

As in our prior trials, we will use a modification of the NIMH Collaborative Study Psychotherapy Rating Scale (CSPRS) [50, 51], which measures the extent of specific therapist behaviors. Original CSPRS items assessing CBT intervention components were retained with items added to assess components specific to our CBT-SAD manual. The CSPRS language was modified to reflect group versus individual therapy. Items pertaining to clinical management were rephrased to reflect LT (as opposed to imipramine). A random sample (25%) of session audio-recordings will be selected from each condition (CBT-SAD or LT) and session number and study therapist (in the case of CBT-SAD). Two trained clinical graduate students, blind to condition and session number, will rate the selected audio-recorded sessions. Inter-rater reliability and success at discriminating between the content of the CBT-SAD and LT conditions and between individual session numbers within the CBT-SAD condition will be computed.

### Relevant concomitant care permitted or prohibited during the trial {11d}

As described in the inclusion/exclusion criteria, stable use of antidepressant medications is permitted during the trial.

### Provisions for post-trial care {30}

One human subjects issue in this work is balancing the need for treatment integrity over the follow-up interval with the need for re-treatment. A rigorous test of our aims requires steps to increase the likelihood that treatment over the follow-up interval is consistent with study treatment (i.e., that LT subjects are encouraged to continue light therapy each fall/winter and that CBT-SAD subjects are encouraged to keep using the skills learned in CBT-SAD on their own without a therapist). However, we recognize that we cannot ethically proscribe treatment in the interim and that we are accountable for directing them to resources if there is a need for re-treatment. We have developed an approach that attempts to balance these issues. (By design, one way we will deal with this is the cross-over at winter 2 for subjects who evidence a SAD recurrence at the winter 2 follow-up).

As a step to increase the likelihood that treatment in the interim is consistent with initial study treatment, we will use standardized procedures for instructing participants at the end of study treatment. The first week of September, we will mail standardized letters, signed by the PI, to all participants treated the winter before prompting them to resume study treatment and to pursue new treatments only if needed. Both the CBT-SAD and LT letters include the same, standardized safety net in providing contact information for local mental health centers and treatment providers should they require more formal treatment. The letter to CBT-SAD-treated participants encourages them to keep using the skills learned in the CBT-SAD treatment on their own (without a therapist). The letter to LT-treated participants encourages them to re-initiate daily LT upon onset of the first depressive symptom in the coming fall/winter by either [1] borrowing one of our light boxes or [2] purchasing a device. Should they wish to purchase their own light box, we provide contact information for LT manufacturers with a list of specifications to match our devices (i.e., full-sized units emitting 10,000-lux cool-white light through UV filter). For either scenario, we ask the participant to identify a professional to whom they could turn in the event of side effects (since we will no longer monitor side effects and make prescription adjustments, as we did during acute treatment). LT participants may choose whether or not to have the PI provide a signed, generic letter that the participant may submit to his or her health insurance company to seek reimbursement for the cost of a light box. Participants crossed from CBT-SAD to LT at winter 2 will receive the standard LT letter the next September (winter 3), and participants crossed from LT to CBT-SAD will receive the standard CBT-SAD letter the next September.

### Outcomes {12} (Table 1)

#### Primary outcome: structured interview guide for the Hamilton Rating Scale for Depression—Seasonal Affective Disorder Version (SIGH-SAD

The SIGH-SAD (42) includes the 21-item Structured Interview Guide for the Hamilton Rating Scale for Depression (HAM-D) and a supplementary 8-item subscale to assess atypical depressive symptoms associated with SAD. A trained rater, blind to treatment condition, will administer the SIGH-SAD at pre-treatment, treatment weeks 1–5, post-treatment, and winter follow-ups. The rater will always begin by asking if any new treatment other than the study treatment has been initiated and if any medications have changed. This will be coded in the database and considered as a possible covariate. A second blinded rater will rate audio-recordings of the SIGH-SADs to assess inter-rater reliability. The depression recurrence (primary outcome) criteria define SAD episode onset or recurrence [62] and were used in our prior trials: total SIGH-SAD score ≥ 20 + HAM-D score ≥ 10 + atypical score ≥ 5. Remission at treatment endpoint is classified by satisfying one or both of the following criteria [62]: (1) pre- to post-treatment reduction in total SIGH-SAD score ≥ 50% + HAM-D score ≤ 7 + atypical score ≤ 7, OR (2) HAM-D score ≤ 2 + atypical score ≤ 10. The same criteria will be applied to winter follow-up remission status by comparing follow-up to pre-treatment scores. We will follow our published SIGH-SAD protocol for item scoring rules, rater training procedures, and resolving rater discrepancies [63]. SIGH-SADs were administered live until March 2020 when we shifted to HIPPA-compliant videoconference due to the COVID-19 pandemic.

**Table 1 Tab1:** Measures and assessment schedule

Measure	Construct assessed	Metric	Pre-TX	Weekly during TX	Mid-TX*	Post-TX*	Winter 2	Winter 3
SIGH-SAD [42] (see description)	SAD recurrence (primary outcome) and remission status, symptom severity	Categorical recurrence status, categorical remission status, score	X	X	X	X	X	X
Beck Depression Inventory-II (BDI-II) [52]	Depression symptom severity, remission status (BDI-II ≤ 8)	Score, categorical remission status	X	X	X	X	X	X
Beck Anxiety Inventory [53]	Anxiety symptom severity	Score	X		X	X	X	X
Dim light melatonin onset (DLMO)	Circadian timing	Clock time (military)	X			X	X	X
Wrist actigraphy and Pittsburgh Sleep Diary [54]	Sleep & circadian timing; daytime activity	Mean mid-point of sleep; mean daily activity count	X			X	X	X
^†^Phase angle difference (PAD)	Circadian timing	DLMO–mid-sleep (from actigraphy)	X			X	X	X
^†^PIPR	Post-illumination pupil response	Net PIPR (red–blue light response)	X		X	X	X	X
^‖^Pupil dilation and sustained frontal gamma-band EEG responses to negative and winter words	Prefrontal engagement as it relates to emotion elaboration and regulation	Mean pupillary and sustained frontal gamma responses 2–10 s following emotional word onset	X		X	X	X	X
^‖^Seasonal Beliefs Questionnaire (SBQ) [32]	Maladaptive thoughts about the seasons and light availability	Score	X		X	X	X	X
^‖^Dysfunctional Attitudes Scale-Form A (DAS) [55]	Depressive schemas	Score	X		X	X	X	X
^‖^Behavioral Activation for Depression Scale (BADS) [56]	Self-reported behavioral activation	Score	X		X	X	X	X
^†^Composite Scale of Morningness (CSM) [57]	Chronotype	Score	X		X	X	X	X
Treatment Credibility Scale [58]	Credibility for the CBT-SAD and LT treatment conditions	Score	X		X	X		
Millon Clinical Multiaxial Inventory—Fourth Edition (MCMI-IV) [59]	DSM-5 personality disorders	Scale scores, possible DSM-5 personality disorders	X					
Quality of Life Enjoyment and Satisfaction Questionnaire (Q-LES-Q) [60]	Quality of life related to: physical health, mood, leisure time activities, social relationships, general activities, work (if applicable), household duties (if applicable), and school/coursework	Score	X			X	X	X
Sheehan Disability Scale (SDS) [61]	Mental-health related impairment in work, social life/ leisure activities, and home life/family responsibilities	Score	X			X	X	X
MOS SF-20 (62)	Health-related quality of life	Score	X			X	X	X
SCID-5-RV major depressive episode criteria	Recurrences between post-treatment and winter 2 and between winters 2 and 3	Categorical recurrence status					X	X

*Repeated in winter 2 if switched to the alternate treatment

^†^Candidate mediator of LT’s effects

^‖^Candidate mediator of CBT-SAD’s effects. TX-treatment

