## Assignment of interventions: blinding

### Who will be blinded {17a}

All study personnel other than the PI, the project coordinator, the project biostatistician, and CBT-SAD group facilitators will be masked to study treatment. Importantly, the trained research assistants who administer the primary outcome measure, the SIGH-SAD, will be blinded. Before each SIGH-SAD administration, the rater will inform the participant to answer the questions about symptoms over the past week without disclosing their treatment assignment. If a participant reveals their treatment assignment during a SIGH-SAD, the interview continues, but the rater marks the interview as unblinded and notes the time during the audio-recording when unblinding occurred. The project coordinator then erases the part of the interview when unblinding occurs, assigns a new (blinded) rater to rate the interview in place of the original interviewer, and avoids scheduling the participant with an unblended rater at future time points. Procedures for maintaining the blind in data management are discussed under the Data Management Plan, below.

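### The masked SIGH-SAD rater collects outside-treatment answers that can hint at the arm before scoring, and the re-rating rule is stated only for explicit disclosure

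*Protocol article*

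**What the plan says.** Under Outcomes {12}, the article states: "A trained rater, blind to treatment condition, will administer the SIGH-SAD at pre-treatment, treatment weeks 1–5, post-treatment, and winter follow-ups". The same paragraph sets the order of the interview: "The rater will always begin by asking if any new treatment other than the study treatment has been initiated and if any medications have changed".

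The section on discontinuing or modifying interventions {11b} says that "we have added relevant questions to the beginning of each SIGH-SAD assessment" and gives the wording: "Have you started any new treatments outside of the treatment you are receiving in this study such as light therapy, talk therapy, or medications". It continues: "If a participant responds affirmatively, they will be queried by the interviewer for the details of this non-study treatment, which will be recorded". The project coordinator checks these answers weekly, and a participant who has started a new treatment counts as withdrawn from the treatment protocol but stays in follow-up and in the intent-to-treat analysis.

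The blinding section {17a} adds two safeguards. Before each interview, "the rater will inform the participant to answer the questions about symptoms over the past week without disclosing their treatment assignment". Then: "If a participant reveals their treatment assignment during a SIGH-SAD, the interview continues, but the rater marks the interview as unblinded". In that case the coordinator erases the relevant part of the recording, a new masked rater's score replaces the original one, and the participant is kept away from the unblinded rater afterwards.

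**The concern.** Participants know their treatment, and the stated aim is to confirm that CBT-SAD is superior. Recurrence depends on three cut-offs on an interviewer-rated scale (total at least 20, HAM-D at least 10, atypical at least 5), so a small shift in scoring can reclassify someone near a threshold. Masking of the rater is therefore an important protection.

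The script asks that rater, before any symptom item, about the two modalities under comparison. A participant can answer truthfully, keep to the instruction not to disclose the assignment, and still give the rater a reason to guess the arm. As written, the remedy is tied to disclosure, so a guess leads to no flag, no second rating and no change of rater at later visits.

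**Working it through.** No figure in the plan is in dispute, so the check is mainly a comparison of provisions, followed by an illustration of size.

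**1. Which interviews can be affected.** Under Screening and enrollment procedures, randomisation comes at the end of the pre-treatment assessment, so the pre-treatment SIGH-SAD is unaffected. Weeks 1–5, post-treatment and the winter follow-ups can be affected.

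**2. Which answers carry information about the arm.**
- A plain no: none, because the question concerns treatment outside the study.
- A medication change: little, because it does not separate the arms.
- Outside light therapy started during acute treatment: suggests CBT-SAD, because LT participants already have a study light box.
- New talk therapy: points weakly towards LT.
- A purchased light box at winter 2: fits either arm. Provisions for post-trial care {30} invites LT participants to resume light by borrowing or buying a device.

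**3. What the safeguards cover.** Section {17a} acts when the participant reveals the assignment. A remark during acute treatment that amounts to disclosure is covered. An inference from an answer about outside treatment is not mentioned.

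**4. Whether the second rater would expose the problem.** Section {12} has a second masked rater score audio recordings. The question opens the interview, and outside the disclosure case the article does not say that this segment is cut. Both raters may hear the same cue, so agreement between them would not exclude bias.

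**5. Scale: the plan's own figure.** Sample size {14} claims 80% power for 28% against 50% with 80 per arm. The article states no alpha; two-sided 5% is assumed. A pooled z-test gives 82.0%, and a Wald test on the log odds ratio gives 80.6%. The smallest detectable difference is 21.4 to 21.5 points, in line with the stated 22. The projected 37 and 22 recurrences imply (37 − 22)/80 = 18.75 points.

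**6. Size of a possible bias (all inputs assumed).** Let both arms have true recurrence p, with 80 per arm. Let a share u of interviews in each arm be cued and not re-rated, and let a fraction m of the LT non-recurrences and CBT-SAD recurrences among them be misclassified in favour of CBT-SAD. Then:
- LT observed = p + u·m·(1 − p)
- CBT-SAD observed = p − u·m·p
- spurious difference d = u·m
- rejection rate = Φ((d − 1.96·se0)/se1) + Φ((−d − 1.96·se0)/se1), where se0 is the pooled and se1 the unpooled standard error.

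Example with p = 0.28, u = 0.10, m = 0.25: LT 0.28 + 0.025 × 0.72 = 0.298; CBT-SAD 0.28 − 0.025 × 0.28 = 0.273; d = 0.025; rejection rate 0.064.

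| u | m | Spurious difference | Type I error (p = 0.40 / p = 0.28) |
|---|---|---|---|
| 5% | 10% | 0.5 points | 0.051 / 0.051 |
| 10% | 25% | 2.5 points | 0.062 / 0.064 |
| 30% | 25% | 7.5 points | 0.161 / 0.179 |

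**The case against.** The strongest reply is that the question is harmless in most interviews and that masking has other support. Much of this stands.

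- A reader might infer that the rater is led to the arm at every interview. The text does not support that: the question excludes study treatment, probing follows only a yes, and the pre-treatment interview precedes randomisation.
- A reader might take a purchased light box as proof of CBT-SAD. At winter 2 it is not, for the reason given in step 2. New talk therapy is also a weak cue then, because the September letters give both arms the same list of providers.
- Masking is not the only protection. Section {12} adds a structured interview, published scoring rules, rater training, a second masked rater and a procedure for discrepancies. Data management {19} adds that participants agree not to discuss treatment with staff other than their interventionist.
- The Aim 1 covariate list, which includes light therapy use in the CBT-SAD group, does not show that raters hear of it. The follow-up procedures collect interim treatment use by questionnaire.
- The only related rate suggests that such answers may be rare: in the prior trial one participant reported a medication change during treatment (Eligibility {10}). That covers medication only, in the acute phase.
- The article is condensed and refers to a published SIGH-SAD protocol for scoring and rater procedures. A rule on inferred assignment may exist there.

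These points limit how often the problem arises and how large it can be. They do not change the order of the interview, the wording of the question or the stated trigger for re-rating.

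**Conclusion.** The point holds in limited form. After randomisation, the masked rater's own script can produce a cue to the arm before the primary outcome is scored, and the stated remedy covers disclosure but not inference.

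The size is unknown. The article gives neither a rate of new treatment nor a rate of unblinding, so the table above rests on assumed inputs. It suggests a negligible to small effect when 5–10% of interviews are affected, and a material one only if cued interviews are frequent and scoring shifts markedly.

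A larger figure should not be read into the documents. If 10–25% of the 160 participants gave a cue, that would be 16–40 interviews, or 8–20 per arm. Five reclassifications in one arm (5/80 = 6.25 points) would then require 5/20 = 25% to 5/8 = 62.5% of that arm's cued ratings to flip. Nothing in the article supports such a rate. This is a worthwhile, low-cost improvement and not evidence that the primary comparison is invalid.

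**What to change.** 1. Take the new-treatment and medication-change questions out of the masked rater's script. Collect them at the same time points by the online survey in use since March 2020 (Data management {19}), or through the project coordinator, who is unmasked, does not conduct outcome assessments and already checks these answers weekly. The BDI-II is due at every SIGH-SAD time point in Table 1, so a self-report occasion exists at each. The treatment-utilisation questionnaires already cover part of this at winters 2 and 3.
2. Keep these questions outside the SIGH-SAD recording, so that the second rater does not hear them.
3. Extend the flag and re-rating in {17a} to interviews in which the rater believes the arm can be inferred.

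The cost is a moved form and a short script amendment, with no extra staff or visits. The covariate and the withdrawal monitoring are kept. There are two small downsides: the rater lacks medication-change information when scoring, and the interview procedure will differ between earlier and later cohorts. The second should be documented by recording the date of the change. With recruitment ending in February 2022 and follow-up in the next two Januaries, the last cohort's winter 2 interviews still lay ahead of the protocol version described.
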